#### Baseline Measures of General Cognitive Functioning

*National Adult Reading Task*. The Danish version of the National Adult Reading Task (DART/NART) (63) assesses verbal crystalized intelligence, which is indicative of general premorbid cognitive functioning. Respondents are asked to read 50 incongruent words in Danish (i.e., the pronunciation does not correspond with how the word is spelled). The total DART score can be converted to an intelligence quotient score (IQ score).

*Montreal Cognitive Assessment*. The Montreal Cognitive Assessment (MOCA) is a short screening tool that is sensitive to mild cognitive impairment. It assesses six cognitive domains: attention, orientation, executive functioning, visuospatial construction, memory, and language (64). The MOCA consists of short cognitive tasks that can be administered in 10 min.

#### Experimental Measures

##### Cue-Induced Cravings

Cravings for alcohol will be assessed by exposing patients to 14 alcohol-related pictures from the AACTP and 14 alcohol-related pictures that were not included in the AACTP. The aim is to determine whether cue-induced cravings will decrease in the experimental AACTP group and whether the decrease is generalized to alcohol-related stimuli not included in the AACTP. Cue-induced cravings in response to the pictures will be measured using (a) self-report by means of a visual-analog scale (see Section 2.6.2.2. for a description) (57, 58) and (b) physiological reactivity by means of skin conductance response using Imotions, which is a computerized system that has been used in various experimental studies.

##### Cognitive Flexibility

The classic Stroop task will be used to measure patients' degree of general attentional control. Task stimuli consisting of two types of words are used: (1) Congruent words comprise the names of four colors (i.e., red, yellow, blue, and green) that are written in a color that is congruent with the name of the color (e.g., the word *red* in red letters); (2) Incongruent words consist of the same four names of colors, but they are presented in a font color that is incongruent with the name of the color (e.g., the word *red* in blue letters). The patient's task is to name the color in which the words are presented while attempting to ignore the meaning of the word. Both the mean reaction time for correctly naming the color of the words and the number of correct responses (mean accuracy) will be recorded. Subtracting mean reaction time to the congruent words from the mean reaction time to the incongruent words gives a measure of the participant's cognitive interference (26).

##### Alcohol Attentional Bias

Patients' AB for alcohol cues will be assessed using the alcohol Stroop task. The task consists of two categories of words presented in different font colors (i.e., red, yellow, blue, and green): (1) alcohol-related words (e.g., bar, beer, rum, scotch, tequila, vodka, whisky), and (2) neutral words (e.g., ceiling, cupboard, fence, gate, shed, tap, chair). The two categories of words are matched for word frequency and length, number of syllables, and semantic relatedness. As in the classic Stroop task, the patient's task will be to name the color in which the words are presented while attempting to ignore the meaning of the words. AB is indicated by longer reaction times to the alcohol-related words relative to the neutral words (27, 32).

In this study, the alcohol Stroop task with pictures will also be used to measure patients' AB for alcohol cues, thereby indicating whether patients have benefitted from the AACTP training. To determine this, the task will consist of pictures of alcoholic and non-alcoholic beverages, each presented with colored outlines (i.e., red, yellow, blue, or green): (1) pictures of alcoholic beverages (e.g., beer, wine, spirits), and (2) pictures of non-alcoholic beverages (e.g., water, orange juice, smoothie). Alcohol AB is indicated by longer reaction times to the alcohol cues than to the non-alcoholic cues (24).

##### Attentional Bias Measured With Eye Tracker

*Multi-stimulus free-viewing task (MSFVT)*. The MSFVT will be used to also measure patients' AB for alcohol cues. The task consists of 54 matrices, each containing pictures of eight alcoholic and eight non-alcoholic drinks. Each matrix will be presented for 6 s. The task consists of three blocks of 18 trials. Unlike the alcohol Stroop task, this task is not based on reaction times; instead, it involves eye tracking. For each matrix, the patient is required to gaze at a fixation dot in the center of the screen for 100 ms for the matrix to appear. After a further 2,000 ms interval, the next fixation dot appears (65, 66). Tracking of the patient's eyes will, like the other physiological measure (skin conductance response), be recorded using Imotions.

##### Alcohol Action Tendency and Inhibition Bias

*Alcohol approach-avoidance task (AAT)*: The AAT measures the degree of alcohol approach bias. During the AAT, patients are requested to react to pictures of the alcoholic drinks by using avoidance responses (i.e., by pushing a joystick away from themselves) and to react to the pictures of non-alcoholic drinks using approach responses (i.e., by pulling a joystick toward themselves). The mean reaction time and the number of correct approach and avoidance responses will be recorded. Similar to AB, approach bias is indicated when reaction times are faster for approaching alcohol cues than for avoiding them, whereas the opposite indicates an avoidance bias (67, 68).

Alcohol Go/No-Go (A-GNG) task: Patients' response inhibition for alcohol cues will be recorded with the A-GNG (69, 70). Here, the patient must respond to pictures of non-alcoholic drinks (e.g., a bottle of coke or of water; the Go stimuli) and inhibit their responses to alcoholic stimuli (e.g., a bottle of beer; the No-Go stimuli). The following indices will be recorded: Number of commission errors (i.e., *false alarms* or erroneously responding to no-go stimuli), omission errors (i.e., *misses* or failing to react on go-stimuli), accuracy (i.e., *hits* or the number of correct responses for go-stimuli), and the reaction times for the trials with correct response on go-trials. A high rate of commission errors would indicate that the patient has reduced inhibitory control, whereas a large number of omission errors would indicate lapses in attention (71). To avoid potential practice effects from the baseline to the post-treatment assessments of the experimental tasks, two parallel versions of the experimental tasks will be used.

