### Measures

Upon admission to the study, patients in all three or the groups will be assessed in a baseline interview. Details about patients' socio-demographic characteristics, AUD diagnosis, treatment goals, and pharmacological treatment will be obtained from their clinical records (54–56). At baseline, the general premorbid intelligence level and cognitive functioning will be assessed. Experimental measures of patients' cue-induced cravings, alcohol AB, action-tendency bias, inhibition bias, and cognitive flexibility (24, 26, 27, 57, 58) will be administered at baseline and post-treatment. Clinical measures of patients' alcohol consumption (the primary outcome measure), cravings, self-efficacy, and affective states (the secondary outcome measures) (57–62) will be taken at the baseline, post-treatment, and follow-up assessments. The follow-ups will be given at 3- and 6-months post-treatment.

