The use of the Internet and mobile devices to deliver a novel treatment to adults might help us improve standard evidence-based treatments for AUD and related disorders (2–4). However, although eHealth-based interventions might have major advantages in terms of increasing availability and reducing the socio-economic burden on society, when targeting clinical AUD populations, these interventions should be delivered only as an add-on for increasing the effectiveness of a treatment that has already been proven to be effective. Because AB for alcohol cues is proportional to the amount of alcohol habitually consumed, and these biases are not addressed within current evidence-based treatment programs, this study is expected to provide new evidence regarding the effectiveness of the gamified AACTP in a clinical population. Furthermore, the intervention should also provide valuable insights into implicit cognitive processes and relationships among alcohol ABs, action-tendency bias (i.e., approach-avoidance bias), and inhibition bias. These implicit processes have all been studied extensively in patients with AUD (16, 25, 87), but there is still a need for more integrative evidence on the associations between the various types of alcohol-related cognitive biases and their role in the maintenance of addictive behaviors (88).

If this study demonstrates that AACTP is effective in patients with AUD, other means of assessing ABs and delivering cognitive training programs could be implemented by utilizing technologies such as virtual reality (VR) and augmented reality [AR; (89)]. These technologies have already been developed for targeting approach biases through the approach avoidance training program (90). Paradigms using VR and AR might overcome some of the shortcomings of the AACTP by increasing its ecological validity. The multimodal nature of these paradigms might cause them to be perceived as closer to real-life situations than other eHealth options (91). Nonetheless, the implementation of VR and AR technologies is an emerging field of research, and the exact implications of their efficacy and effectiveness in treatments targeting AB in AUDs are yet to be examined (91).

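### The approach-avoidance task as described contains no instructed alcohol-approach trials, so it contradicts the approach-bias index defined in the same paragraph

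*Protocol article*

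**What the plan says.** All of the task detail is in one paragraph of the protocol article, under Experimental Measures, Alcohol Action Tendency and Inhibition Bias.

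- Instruction for alcoholic pictures: "patients are requested to react to pictures of the alcoholic drinks by using avoidance responses", that is, a push of the joystick.
- Instruction for non-alcoholic pictures: "to react to the pictures of non-alcoholic drinks using approach responses (i.e., by pulling a joystick toward themselves".
- Data kept: "The mean reaction time and the number of correct approach and avoidance responses will be recorded".
- Score: "approach bias is indicated when reaction times are faster for approaching alcohol cues than for avoiding them". The reverse pattern is read as an avoidance bias.

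At the end of the section, after the Go/No-Go task, the article adds that "two parallel versions of the experimental tasks will be used", with the stated purpose of limiting practice effects between baseline and post-treatment.

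The Measures section places the construct among the variables assessed at baseline and post-treatment: "Experimental measures of patients' cue-induced cravings, alcohol AB, action-tendency bias, inhibition bias, and cognitive flexibility". The Discussion expects the trial to give "valuable insights into implicit cognitive processes and relationships among alcohol ABs, action-tendency bias" and inhibition bias.

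**The concern.** The index compares two reaction times to the same kind of picture: approaching alcohol and avoiding alcohol. The instruction ties each kind of picture to a single movement, so one of those two reaction times is never collected on an instructed trial. Anyone who programmed the task from this text would have no value for the stated score. They could fall back only on a comparison in which picture and movement change together.

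At stake is one of the three bias constructs whose relationships the Discussion says the trial will inform. If the fallback comparison were reported as approach bias, a difference between groups could not be attributed to a change in action tendency.

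**Working it through.** The protocol gives no figure to reproduce. The check is whether the stated index can be estimated from the cells that the instruction creates.

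**Step 1: lay out the cells.** Inputs are the two instructions in the task paragraph.

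| Picture | Approach (pull) | Avoid (push) |
|---|---|---|
| Alcoholic | not described | instructed |
| Non-alcoholic | instructed | not described |

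Two of four cells are observed.

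**Step 2: write the index as a contrast.** Order the mean reaction times as (alcohol approach, alcohol avoid, non-alcohol approach, non-alcohol avoid). A contrast is estimable only if it is a linear combination of the observed cells, here (0, 1, 0, 0) and (0, 0, 1, 0).

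| Contrast | Weights | Task as described | All four cells |
|---|---|---|---|
| Stated index: alcohol approach − alcohol avoid | (1, −1, 0, 0) | not estimable | estimable |
| Double difference: the stated index minus the same contrast for non-alcohol | (1, −1, −1, 1) | not estimable | estimable |
| Non-alcohol approach − alcohol avoid | (0, −1, 1, 0) | estimable | estimable |

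The first two contrasts put non-zero weight on a cell that is never observed. Adding more trials of the described kind does not change this.

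**Step 3: ask whether a simpler model helps.** Suppose content and movement only add: RT = b0 + b1·(alcohol) + b2·(approach). The observed cells give the rows (1, 1, 0) for alcohol push and (1, 0, 1) for non-alcohol pull. The rank is 2 for 3 parameters. The difference between the cells is (b0 + b2) − (b0 + b1) = b2 − b1. Adding any constant d to both b1 and b2, and subtracting d from b0, leaves both cell means unchanged. The approach effect b2 is therefore not identified even without an interaction.

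**Step 4: look for the missing cell elsewhere in the text.**

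- Wrong movements: a pull to an alcoholic picture may occur, but under the stated instruction it is an error. It is not the instructed approach response that the index needs.
- Counts of correct responses: these are still recorded, but they carry the same confounding of content with direction.
- Parallel versions: they are introduced against practice effects, and no reversed instruction is mentioned.
- Measures and Discussion: both name the construct without describing the task further.

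Nothing in the document supplies alcohol-approach trials.

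**Step 5: trace what depends on the score.** The primary outcome is weekly mean drinking from the timeline follow-back. Action-tendency bias is not among the listed secondary outcomes and is not named in the Aims. In Statistical Analysis, the hypothesised mediators are alcohol attentional bias and craving, and the ancillary interactions concern drinking history, affective states and cognitive flexibility. No effect size for action-tendency bias enters the sample-size reasoning.

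**The case against.** The strongest reply is that this is a journal article. It gives the task a single instruction sentence and cites sources for the index. The index itself presupposes alcohol-approach trials, so the real task may well include a block with the mapping reversed that was lost in condensing. This stands as a limit on the conclusion: the text shows a defect in the task as described, not in the task as programmed. It does not remove the point. The article does more than leave out detail. It states a one-to-one pairing and a score that cannot both hold.

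A second reply is that randomisation makes any between-group comparison fair, including one on the fallback contrast. That is true for the contrast itself, but a difference in b2 − b1 still cannot be labelled approach bias.

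Three stronger readings are tempting, and the document does not support them.

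- A reader might infer that the outcome is lost for all 317 patients at both assessments. The task script is not shown, so loss is not established. Moreover, 317 is the baseline number, which allows for 20% attrition from the 264 needed for analysis (264 + 264 × 0.20 = 316.8), so not all 317 are expected to complete later assessments.
- A reader might infer that pushing alcohol away at each assessment trains avoidance and so biases the trial. No trial count is given, and the exposure is the same in all three groups, so it does not explain a between-group bias.
- A reader might infer that the efficacy conclusions are in doubt. None of the stated ones rests on this score.

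**Conclusion.** The point holds as an internal contradiction. Read literally, the described task has 0 instructed alcohol-approach trials, the stated index is undefined, and the only available contrast mixes picture content with movement direction. This rests on the article's instruction being the whole instruction; if a reversed block exists, the error lies in the description alone. Either way the text needs changing. The reach is limited to one experimental measure at two assessments. The primary outcome, the listed secondary outcomes, the named mediators and the sample size are untouched. It should be corrected, but it does not threaten the main question of the trial.

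**What to change.** Reconcile the task instruction with the index.

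1. If the programmed task already includes alcohol-approach trials, correct the description to say so. This costs a sentence or two.
2. If it does not, add them. Alcohol-approach trials are the minimum that makes the stated index computable. The better choice is to run alcoholic and non-alcoholic pictures each with push and pull, in counterbalanced blocks. The alcohol contrast can then also be set against the non-alcohol contrast, which separates a bias toward alcohol from a general difference between pulling and pushing.
3. If any patients have been assessed with the fixed pairing, report their result as non-alcohol pull against alcohol push, and do not call it approach bias.

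The cost of the second step is re-scripting a computer task and possibly a slightly longer assessment. The article gives neither trial counts nor duration for this task, so the added time cannot be stated.

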#### Clinical Outcomes

##### Primary Outcome Measures

Alcohol consumption will be measured with the Alcohol Timeline Follow-back (TLFB) method. It involves using a calendar to help the patient retrospectively recall the number of drinks that he/she consumed on each day during the previous 3 months (59, 72). The results will be used to calculate various alcohol consumption measures, including weekly mean drinking, which will be the primary outcome measure.

To validate the TLFB, hair samples from the patients will be tested for ethyl glucuronide (ETG) by liquid chromatography-tandem mass spectrometry (LC-MS/MS). This biological marker of alcohol consumption will be collected and analyzed according to the Society for Hair Testing (73, 74).

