## Abstract

**Background:** There is consistent evidence that community and clinical samples of individuals with an alcohol use disorder (AUD) have attentional biases toward alcohol cues. The alcohol attentional control training program (AACTP) has shown promise for retraining these biases and decreasing alcohol consumption in community samples of excessive drinkers. However, there is a lack of evidence regarding the effectiveness of ACTP in clinical AUD samples. The main aim of the present study is to investigate whether primary pharmacological and psychological, evidence-based alcohol treatment can be enhanced by the addition of a gamified AACTP smartphone application for patients with an AUD.

**Design and Methods:** The study will be implemented as a randomized controlled trial. A total of 317 consecutively enrolled patients with AUD will be recruited from alcohol outpatient clinics in Denmark. Patients will be randomized to one of three groups upon initiation of primary alcohol treatment: Group A: a gamified AACTP smartphone application + treatment as usual (TAU); Group B: a gamified AACTP sham-control application + TAU; or Group C: only TAU. Treatment outcomes will be assessed at baseline, post-treatment, and at 3- and 6-month follow-ups. Repeated measures MANOVA will be used to compare the trajectories of the groups over time on alcohol attentional bias, alcohol craving, and drinking reductions. It is hypothesized that Group A will achieve better treatment outcomes than either Group B or Group C.

**Perspectives:** Because attentional bias for alcohol cues is proportional to the amount of alcohol consumed, and these biases are not addressed within current evidence-based treatment programs, this study is expected to provide new evidence regarding the effectiveness of the gamified AACTP in a clinical population. Furthermore, due to promising results found using AACTP in community samples of excessive drinkers, there is a high probability that the AACTP treatment in this study will also be effective, thereby allowing AACTP to be readily implemented in clinical settings. Finally, we expect that this study will increase the effectiveness of evidence-based AUD treatment and introduce a new, low-cost gamified treatment targeting patients with an AUD. Overall, this study is likely to have an impact at the scientific, clinical, and societal levels.

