### Primary Treatment at the Outpatient Alcohol Clinics

At treatment entry, patients will be offered detoxification, if needed, before their primary treatment at one of the outpatient clinics is initiated. The primary treatment lasts 3 months and consists of both a pharmacological and a psychological treatment. The pharmacological treatment includes treatment with disulfiram and acamprosate. Naltrexone or nalmefene is also offered when deemed appropriate. The psychological treatment consists of cognitive-behavioral therapy (CBT), which is provided during hour-long individual or group sessions and typically includes eight sessions. The therapist and patient jointly plan the course of the patient's treatment. The treatment typically includes psychoeducation, functional analysis of drinking situations, and the development of coping strategies. The strategies include waiting out until an urge passes rather than acting on it, thinking about the negative consequences of drinking, thinking about the positive consequences of sobriety, consuming healthy alternative foods and beverages, problem-solving, and homework assignments between sessions. Therapists conduct the psychological treatment; they include nurses and social workers who have been specifically trained to deliver the range of therapies. Supervision takes place frequently, and psychiatrists regularly monitor patients' progress during the treatment (47).

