### Recruitment

Based on a power calculation (see Section 2.7.), a total of 317 patients will be required for the data analysis. On the basis of data from the Danish National Alcohol Treatment Register (48) and prior studies conducted at this clinic (49–52) and prior studies of AACTP (32, 36, 42), it seems feasible that at least 317 eligible patients (see Section 2.4.) can be recruited from January 2021 to July 2022.

After completing detoxification and prior to starting primary treatment, each patient will be briefly informed about the project and asked whether he or she is willing to meet with a research assistant who will provide further information about the study. If the patient agrees, the research assistant will provide the patient with oral and written information about the details of the study. After informed consent has been provided, a baseline interview will be conducted, and each patient meeting the eligibility criteria will be randomized. To minimize the risk of bias and to overcome potential group imbalances, the current study will utilize an urn technique that will randomize the patients to one of the three treatment groups.

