### Eligibility Criteria

To be eligible to participate, patients must fulfill the following criteria. They must (1) sign written informed consent, (2) be between 18 and 65 years old (because the intervention is web-based), (3) be fluent in Danish, (4) have completed detoxification (if deemed appropriate), (5) have been admitted to primary treatment within the past 8 weeks, (6) not be color-blind, (7) not have a severe psychiatric or neurological illness (e.g., a psychotic disorder, intellectual disability, dementia) or terminal physical illness.

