### Experimental and Control Groups

The 317 patients (see power analysis below) fulfilling the eligibility criteria will be randomized to one of the three groups: Group A: AACTP delivered *via* a smartphone application + treatment as usual (TAU; *n* = 106), Group B: ACTP sham training delivered *via* a smartphone application + TAU (*n* = 106), or Group C: TAU only (*n* = 106). Patients in Group A will receive seven sessions of AACTP (one session per week for 7 weeks). Patients in Group B will receive seven sessions of sham training (one session per week for 7 weeks). Patients in Group C will receive only the primary treatment for AUD. Patients in the AACTP and sham control groups will start the primary treatment within the 1st month of their admission, so that the add-on treatment will not extend beyond the 3-month treatment period.

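### The 3-month drinking recall at the post-treatment visit can reach back before randomisation for patients who enter after treatment has started, and the entry statements conflict

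*Protocol article*

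**What the plan says.** All references are to the Protocol article.

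- **Outcome window.** Under Primary Outcome Measures, patients "retrospectively recall the number of drinks that he/she consumed on each day during the previous 3 months". The interview yields several consumption measures, "including weekly mean drinking, which will be the primary outcome measure". Under Measures, it is taken at baseline, post-treatment, and 3 and 6 months after post-treatment.
- **Length of treatment.** "The primary treatment lasts 3 months" (Primary Treatment at the Outpatient Alcohol Clinics). Groups A and B receive seven sessions, one a week.
- **Entry.** Four places describe it:
  - Abstract: "Patients will be randomized to one of three groups upon initiation of primary alcohol treatment".
  - Recruitment: patients are approached "After completing detoxification and prior to starting primary treatment", and randomisation follows consent and the baseline interview.
  - Eligibility Criteria: patients must "have been admitted to primary treatment within the past 8 weeks".
  - Experimental and Control Groups: patients in Groups A and B start within the first month of admission, "so that the add-on treatment will not extend beyond the 3-month treatment period". The text names primary treatment as what starts then; the context suggests that the add-on is meant.
- **Test.** Under Statistical Analysis, efficacy is judged by the time-by-group interaction over the four assessments.

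**The concern.** The recall window and the primary treatment are equally long. A patient randomised some weeks into treatment and assessed at its end therefore reports, as post-treatment drinking, some weeks that came before randomisation. Those weeks were also reported at baseline. They cannot differ between arms because of the intervention, so they pull the post-treatment comparison toward zero, and by an amount that varies with each patient's entry date. For late entrants the baseline value also mixes drinking before treatment with up to 8 weeks of drinking on treatment.

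The affected time point matters. The protocol's Discussion reports that in the earlier web-based trial the consumption effect was not maintained at 3 months, and that in another trial the reductions had attenuated by 6 months. On that evidence, post-treatment is where an effect is most likely to be seen.

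**Working it through.** **Inputs.** Recall window 3 months; primary treatment 3 months; entry at 0, 1 month (Experimental and Control Groups) or 8 weeks (Eligibility Criteria); training 7 weeks. One month = 365.25/12/7 = 4.35 weeks, so 3 months = 13.04 weeks.

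**The plan's own timing.** Starting within the first month keeps the add-on inside the 3 months: 4.35 + 7 = 11.35 ≤ 13.04. This reproduces.

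**The same check for an 8-week entrant.** 8 + 7 = 15 > 13.04. Counting only the six intervals between seven sessions, 8 + 6 = 14 > 13.04. The eligibility rule and the stated limit on the add-on cannot both hold for such a patient.

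**Share of the post-treatment window before randomisation.** Share = max(0, 13.04 − weeks from randomisation to the visit) / 13.04.

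| Visit date assumed | Entry | Weeks randomisation to visit | Weeks before randomisation | Share |
|---|---|---|---|---|
| End of primary treatment | Treatment start | 13.04 | 0 | 0% |
| End of primary treatment | 1 month | 8.70 | 4.35 | 33% |
| End of primary treatment | 8 weeks | 5.04 | 8.00 | 61% |
| End of 7 weeks of training begun at randomisation | Any | 7.00 | 6.04 | 46% |

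**Effect on power for the post-treatment contrast alone (illustration).** Model: change from a 13-week baseline mean to a 13-week post-treatment mean; weekly errors with first-order autocorrelation; the effect acts only after randomisation; every patient has the same overlap of s weeks; power is 90% when s = 0. Power = Φ(3.242 × r − 1.96), where 3.242 = 1.96 + 1.282 and r is the ratio of effect to standard deviation relative to s = 0.

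With autocorrelation 0, shared weeks cancel in the change score. The effect scales as (13 − s)/13 and the variance as 2(13 − s)/169, so r = √(1 − s/13):

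- s = 4 (31%): r = √0.692 = 0.832, power 0.77.
- s = 6 (46%): r = √0.538 = 0.734, power 0.66.
- s = 8 (62%): r = √0.385 = 0.620, power 0.52.

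Over assumed autocorrelations of 0, 0.5, 0.8 and 0.95, the ranges are 0.77–0.83, 0.66–0.80 and 0.52–0.77.

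**Effect of restricting to days after randomisation.** With autocorrelation 0, the variance becomes 1/(13 − s) + 1/13, against 2/13 for s = 0, and the effect is undiluted:

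- s = 4: r = √(0.1538/0.1880) = 0.904, power 0.83 (unmodified 0.77).
- s = 8: r = √(0.1538/0.2769) = 0.745, power 0.68 (unmodified 0.52).

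Using all days after randomisation beat the unmodified window at every overlap and autocorrelation tried. A fixed window of the last 4 weeks did not: at s = 4 it gave 0.60–0.81, below the unmodified 0.77–0.83.

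**The case against.** The strongest reply is that the problem may not arise. The Abstract and the Recruitment section put randomisation at or before the start of treatment; with a visit at the end of the 3 months, the overlap is then zero. The article is also condensed, and a recall period used to collect data need not be the period averaged, so a full analysis plan may already restrict the window. This stands as a limit on size. It does not remove the point, because the printed eligibility rule permits later entry, and the conflict among the entry statements is in the text itself.

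A reader might infer several stronger things that the documents do not support:

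- **That all patients are affected, or about 31% of the window on average.** The average needs entry spread evenly over 0 to 8 weeks, which is nowhere stated. The 46% for everyone needs the visit to be timed from the end of training begun at randomisation. Group C has no training, so that cannot date its visit.
- **That power collapses to 0.61, 0.42 or 0.23** (at 31%, 46% or 62%). These figures hold the standard deviation constant, although shared days cancel in a change from baseline. They also apply the planned 90% to a single contrast, whereas the protocol computed it for the repeated-measures MANOVA.
- **That the comparison is biased between arms.** Drinking before randomisation is balanced in expectation.
- **That Groups A and B have a different entry rule from Group C.** Eligibility is settled before randomisation, so the first-month statement is better read as scheduling for the arms that have an add-on.
- **That the mediation analysis is invalid.** The protocol does not name post-treatment drinking as the mediated outcome.

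**Conclusion.** The point holds in a conditional form. On the printed rules, up to 8 of 13 recalled weeks (about 61%) at the first post-baseline assessment of the primary outcome can precede randomisation; this is the worst case with a visit at the end of primary treatment. The share is about 33% for entry at 1 month and 0% for entry at treatment start. The consequence is dilution of the post-treatment contrast toward the null, with no type I error inflation and no effect on the 3- and 6-month windows.

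The power ranges rest on an assumed error structure and on all patients sharing the same overlap. They describe one contrast; the loss for the interaction test was not computed and depends on the actual distribution of entry dates. Separately, the four entry statements cannot all apply, and the 8-week rule is incompatible with the stated limit on the add-on.

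**What to change.** 1. Compute post-treatment weekly mean drinking from all recalled days after randomisation, up to 3 months, rather than from a fixed last-30-day window.
2. Leave the 3- and 6-month windows at 3 months; shortening them would discard clean data.
3. End the baseline window at randomisation.
4. Date the post-treatment visit by one rule that applies identically to all three arms.
5. Reconcile the Abstract, Recruitment, Eligibility Criteria, and Experimental and Control Groups into one entry rule consistent with the limit on the add-on. Which rule is right is for the investigators.

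The recall is recorded day by day, so this needs no new data: one derivation rule and a clarifying amendment, settled before analysis. The cost is a shorter and somewhat noisier post-treatment window for late entrants, about 5 weeks for an 8-week entrant assessed at the end of treatment.
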